### Intervention arm

The EIP is a community-based, peer-led group programme with caregivers at a community level, using a participatory approach driven by adult learning theory.^16^ The programme manual is freely available to download (https://www.ubuntu-hub.org). Development of the programme is described in box 2.

Box 2Developing the ABAaNA early intervention programme (EIP)In low-income and middle-income countries, services for affected children are often lacking and parental levels of knowledge and understanding about cerebral palsy are often low. To fill this gap, a parent training programme called ‘Getting to Know Cerebral Palsy’ was developed and launched in partnership between the London School of Hygiene & Tropical Medicine and Christian Blind Mission an international disability and development organisation. The programme aims to increase parental knowledge and skills and promotes a participatory learning approach with an emphasis on the empowerment of caregivers across a broad spectrum of impairment for children aged 2–12 years.^23 24^
Since 2011, the ABAaNA studies (‘Abaana’, meaning ‘children’ in the local language Luganda) have been examining risk factors for, and outcomes from, neonatal encephalopathy (NE) in Uganda.^15^ Studies examining early neurodevelopmental outcomes after NE revealed a high prevalence of neurodevelopmental impairment (NDI) with 25% of those affected also having malnutrition from related feeding difficulties.^15^ Qualitative work highlighted the stigma and broad-ranging social, emotional and financial impacts on affected families.^3^
In response, the ABAaNA EIP was developed around the principles of ‘Getting to Know Cerebral Palsy’ (http://www.ubuntu-hub.org), and has been adapted for younger children aged 0–2 years following an iterative process following Medical Research Council recommendations on development and evaluation of complex interventions^25^; it was supported by a diverse Expert Advisory Group including local parents with children with NDI, Disabled Persons Organisations and experts in early intervention and child development. Core themes running through the programme are summarised in figure 2. The newly developed programme was piloted among 28 families at Mulago Hospital in Kampala in 2015–2016 and showed a 25% improvement in family quality of life scores (Paediatric Quality of Life tool, Family *Impact* module 2.0) post intervention (verbal communication).

**Figure 2 F2:**
[figure not shown]
Core themes and content of the ABAaNA early intervention programme.

Participating families are encouraged to share experiences through discussion and reflection, prioritise problems and identify solutions together. Facilitators of the group sessions are ‘expert parents’, themselves parents of children with NDI, who have undergone 5 days of core training followed by regular supervision, face-to-face mentoring meetings and telephone discussions with existing in-country master facilitators (trained therapists in Uganda). Each EIP group involves 6–10 families; groups are selected depending on locality for ease of attendance. The training is divided into 10 modules covering understanding disability, positioning and carrying, feeding, mobilising, communication, play, everyday activities and experiences in the local community (figure 2, table 1). Individual module sessions are delivered every 1–2 weeks and last 2–3 hours including time for facilitated discussion; the entire programme is designed to be delivered over 6 months including at least one home visit conducted by the expert parent facilitator.

**Table 1 T1:** Description of the programme modules

Module	Content
1.Let’s get started	Content and ground rules of the programme Understanding cerebral palsy, additional resources for information Personal stories
2.Know your child	Developmental milestones for young children Determining each child’s progress
3.Positioning and carrying	The importance of optimal positioning Practical skills regarding optimal positioning
4.Eating and drinking	Feeding challenges for children with neurodevelopmental impairment Practical skills for addressing feeding challenges
5.Learning to move	Understanding different types of movement Practical skills for assisting learning to move
6.Communicating	The importance of communication Practical advice to encourage their child to communicate
7.Play and early stimulation	The importance of early stimulation and play for children to develop Challenges of inclusion in play with the family and community Creation of simple toys How parents/ caregivers can encourage their child to play
8.Everyday activities	Using everyday activities to promote child development Management of seizures Review of previous sessions
9.Our community	Community resources available Discussion around barriers to inclusion, addressing stigma and discrimination Understanding disability rights Thoughts and feelings of the caregiver Members of community invited to attend this session
10.Next steps	Planning to facilitate their own group Reflection on learning points Endpoint data collection

#### Fidelity and adherence to the intervention

EIP facilitators will receive a 5-day training programme delivered by two master facilitators, which includes facilitation skills, knowledge transfer on the core contents of the EIP manual and translation of knowledge to practice through simulated sessions with families and children with NDI. All trial intervention groups will be co-facilitated by a master facilitator providing supportive supervision to new facilitators. After each modular group meeting, a short-facilitated feedback session will be conducted, and the content of the module delivered will be recorded. Attendance of individual caregivers and children at the group sessions will be recorded. Facilitators will emphasise to caregivers the importance of attending all sessions, with phone calls prior to each session to promote adherence. If missed, a catch-up session may be offered before the next module.

### Standard care arm

SC refers to care that is currently available in established local services. In both sites, this includes referral to physiotherapy, seizure management and nutritional support. Information on access to local medical, therapy and family services will be collected. Families in the SC arm will be offered delayed entry into the EIP after completing the 18-month assessment. Contamination of the SC arm by exposure of SC families to intervention will be monitored and reported.

### Outcomes

Participants in both arms will be assessed by study staff masked to trial allocation at two time points; at age 12–17 months (which corresponds to completion of the EIP in the intervention arm, 6 months after recruitment) and again at age 18–23 months (12 months after recruitment). (figure 1). Caregivers will be phoned a week before the follow-up assessments to arrange a time for interview. Assessments will be primarily conducted in the study-site clinics. Where caregivers cannot be contacted by phone or are unable to attend the clinic, a community visit will be arranged, and assessments completed at home. Outcome assessments will be conducted by Mulago assessors for children recruited at Kiwoko, and vice versa to ensure assessors are blind to allocation arm. Two assessors will independently assess a small proportion of the children and inter-rater reliability will be calculated.

#### Primary outcome measures

The primary outcomes of the study will be:

*Feasibility of participant recruitment and randomisation* as assessed by the total number recruited and randomised to each arm. Qualitative tools will also be used to capture information on feasibility.
*Acceptability of the EIP among caregivers and healthcare workers* as assessed by the protocol violation rate (eg, participants in the intervention arm being treated as if they were in the control arm or vice versa) at programme completion, and by the number of programme sessions attended between baseline and programme completion. Qualitative tools will also be used to capture information on acceptability.
*Preliminary evidence of impact on family*
*QoL* as assessed using the scored Paediatric Quality of Life (PedsQL) Family Impact module.^17^ The PedsQL comprises 36 items scored on a 0–4 Likert scale and linearly transformed to a 0–100 scale, with higher scores indicating a better QoL. It will be translated into the local language Luganda and administered as a standardised structured interview by trained study staff.

#### Other outcomes of interest

*Child motor functioning* as assessed by the mobility score of the Paediatric Evaluation Disability Inventory (PEDI).^18^ The PEDI is a standardised test designed to identify and describe functional impairment and monitor progress. Normative scaled scores are obtained for children≥6 months to provide age-related expectations of ability.
*Child cognitive function* as assessed by the GMDS.^13^

*Child growth, health and well-being* assessed using weight, height and head circumference measured according to standardised protocol. Occipitofrontal head circumference (paper tape measure), weight (SECA336 electronic scales, Hamburg, Germany) and height will be taken by study staff using standardised procedures. Haemoglobin will be determined on a finger prick sample using HemoCue Hb 201 (HemoCue AB, Angelholm, Sweden). A structured maternal interview in Luganda will report on caregivers concerns regarding health, growth and development of their child and episodes of illness including seizures and other neurological problems, feeding difficulties, chest infections and treatment for malnutrition.
*Caregiver psychological distress* assessed using the Self-Referral Questionnaire (SRQ) and the Parenting Stress Index (PSI).^19^ The SRQ consists of 20 items each scored 0 (symptom absent) or 1 (symptom present) giving a total out of 20. The PSI is a 120-item inventory measuring the magnitude of caregiver stress attributable to parent–child relationship (Total Stress Scale), and situational/demographics factors outside the parent–child relationship (Life Stress Scale). These tools will be translated into Luganda.
*Caregiver–child attachment* assessed using the Maternal Infant Responsiveness Instrument; a 22-item scale designed to measure the parent’s feelings about their infant and an appraisal of the infant’s responses.^20^

*Quality of the home environment* assessed using the Infant Toddler-Home Observation for the Measurement of the Environment. This comprises 45 items, based on observation and/or interview, assessing the physical environment of the home and the child’s interaction within it.^21^

*Cost of illness and protective effectiveness* will be assessed (separate protocol, [name] *et al*).

### Qualitative methods

In-depth interviews (IDIs) will be conducted with five randomly selected caregivers from each arm at each site. Focus group discussions (FGDs) will be conducted with caregivers, at baseline, 6 months post recruitment and again 6 months later in both the intervention and SC arms. Among intervention arm families, qualitative techniques will be used to capture information on the feasibility, acceptability and impact of the EIP intervention using qualitative tools including FGDs, IDIs and observation.

We will describe the experiences of children and caregivers relating to the intervention received including the impact of the disability, parental confidence level, inclusion in community life and experience of stigma and discrimination. We will examine changes in these domains over the follow-up period and explore attributions of change. In addition, we will perform social mapping of parent networks and group discussions with staff on their perspectives and experiences of using the EIP. The themes guiding our analysis will be drawn from objectives of the trial and from the data, should additional areas of interest emerge during interviews and discussions.

The interviews will be conducted by social scientists who have experience in qualitative research.

### Data management and access

Data collected in the clinic or at field visits will be entered on standard clinical record forms (CRFs). Clinical data will be recorded under a unique study ID number. Completed CRFs will be checked by and double entered into a trial-specific MS Access database. Data from both IDIs and FGDs will be collected in the form of audiotapes, transcripts and field notes. All data entry and data management will be overseen by a statistician/data manager at the MRC/UVRI Unit. Data will be maintained on the host institution server and backed up following standardised operating procedures. Paper CRFs will be stored in lockable filing cabinets at the sites. Access to these data during the trial will be restricted to essential personnel (the principal investigators, site co-investigators, medical research officers and data clerks).

#### Confidentiality

All research team members will receive training in confidentiality. Data will be stored without personal identifiers, except where names must be included to ensure identification of the correct participants for procedures. All data will be stored on password-protected computers, accessible only to research team members.

### Sample size

The trial will recruit 126 children and their caregivers, 63 per arm. Allowing for a 20% dropout rate, this sample size will give 90% power to detect a minimal relative difference of 20% on PedQL Family Impact score between the intervention and control arms, at 5% significance level, assuming a mean PedQL score of 65 in the SC arm and SD of 20 in both arms. Assumptions are based on data from the pilot study showing a mean caregiver PedQL score for families before the intervention of 64.9 (SD 19.6) and mean score of 78.9 for families after receiving the intervention (SD 17.5).

### Statistical analysis

The first primary outcome, feasibility of participant recruitment and randomisation, will be assessed by the total number recruited and randomised to each arm. Recruitment and randomisation feasibility will be demonstrated if the target sample size of 126 is achieved. Data on participants screened, eligible and randomised will be displayed in a Consolidated Standards of Reporting Trials flow chart. Descriptive statistics (frequencies, means, medians, SD and IQRs) will be used to describe the sample at baseline, by trial arm.

The second primary outcome, acceptability, will be assessed quantitatively by (1) calculating the protocol violation rate and (2) summarising the number of programme sessions attended between baseline and programme completion for those in the intervention arm. Protocol violation rate will be calculated as the number of participants for whom one or more protocol violations occur divided by the total number of participants, and will be presented both overall, and by trial arm. For participants in the EIP trial arm, the overall number of modules attended by each participant will be tabulated. Acceptability on the basis of number of programme sessions will be defined as attendance of at least six modules.

For the third primary outcome and secondary outcomes, analyses will compare outcomes between intervention and control arms at the end of the programme, when the participants will be aged 12–17 months, and again 6 months later. Analysis will be on an intention-to-treat basis and missing data will not be imputed. Data for each outcome measure will be summarised by trial arm, using proportions for binary outcomes and means or medians for quantitative outcomes, depending on normality of the distribution. Differences in means/proportions between trial arms together with 95% CIs will be calculated. We do not plan any formal statistical tests due to the preliminary nature of the trial; instead CIs will provide a possible range of effect sizes. Regression models (linear regression for continuous outcomes, logistic regression for binary outcomes) will be used to adjust comparisons for baseline measures of the outcomes, which were collected at enrolment into the trial, in order to improve precision of effectiveness estimates. For skewed continuous outcomes, data will be normalised before analysis using suitable transformations or quantile regression will be considered. No subgroup analyses are planned.

Qualitative data will be analysed using a thematic framework approach. Themes will be based on the study objectives and those emerging from the data. Social scientists (two people) will agree the coding frame and undertake analysis collaboratively to ensure agreement on the coding approach. Thematic summaries will be developed and shared with the wider team for discussion.

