### Trial management, data monitoring and reporting of adverse events

The Trial Steering Committee (TSC)^22^ will oversee progress of the study towards its objectives, review relevant information from other sources (eg, other related trials) and receive reports from the Data and Safety Monitoring Board (DSMB). All adverse events, whether related to the intervention or not, will be noted and reported. A Data Monitoring and Safety Committee has been established independent of the investigators and the TSC but reporting to the TSC and the sponsor. The DSMB includes an expert on global child heath, a senior statistician and a senior academic working in newborn and early child health research in Uganda, independent of the investigators. The DSMB will have access to all data on request. Resulting from the initial meeting of the DSMB on 28 June 2017, no formal stopping rules will be applied.

Children with NDI and particularly those with seizure disorders and difficulties with swallowing are at increased mortality risk. All adverse events, whether related to the intervention or not, will be investigated and reported according to the UVRI Research Ethics Committee (REC) in accordance with good clinical practice requirements. All deaths, hospitalisations and other serious adverse effects will be reported to the relevant ethics committee irrespective of whether the death or event is related to disease progression or not. Trial data monitoring will be conducted by an internal independent monitor at initiation, 6 months into data collection, again after 1 year and end of data collection.

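### The planned 12-month quality-of-life comparison uses only families seen at 12 months and leaves the 6-month scores of later dropouts unused, so arm-specific loss after month 6 can bias it

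*Protocol article*

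**What the plan says.** The Statistical analysis section sets the missing-data rule in one sentence: "Analysis will be on an intention-to-treat basis and missing data will not be imputed". The arms are compared "at the end of the programme, when the participants will be aged 12–17 months, and again 6 months later", that is, 6 and 12 months after recruitment. The estimator is also named: "Regression models (linear regression for continuous outcomes, logistic regression for binary outcomes) will be used to adjust comparisons for baseline measures of the outcomes". No model that takes both visits together is mentioned. Inference is by confidence interval only: "We do not plan any formal statistical tests due to the preliminary nature of the trial".

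Under Objectives and hypotheses, the hypothesis on the PedsQL Family Impact module is set at 12 months. The Sample size section gives the size ("The trial will recruit 126 children and their caregivers, 63 per arm") and the allowance for loss ("Allowing for a 20% dropout rate").

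The Outcomes section provides, for both arms, a phone call a week before each follow-up and a home assessment for families who cannot be reached or cannot come to the clinic.

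**The concern.** A linear regression at one visit, with nothing imputed, can use only families with a score at that visit. The article never calls this an available-case analysis, but its two stated choices lead to one. The treatment estimate is then unbiased only if, given arm and baseline score, being missing is unrelated to the outcome.

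At 12 months this ignores useful information. A family seen at 6 months and lost afterwards has a recent score that says a good deal about where it would have been at 12 months, and the 12-month regression does not use it. If families doing badly at 6 months leave more often in one arm than in the other, the remaining families are no longer comparable.

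Such a difference is plausible. EIP families have group sessions every 1–2 weeks, a call before each session and at least one home visit. The study contact described for SC families is the follow-up call and visit that both arms receive.

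Family quality of life is one of three primary outcomes, and the confidence interval for the difference is meant to show the range of effects when a larger trial is designed. A shifted interval serves that purpose badly.

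**Working it through.** **1. The plan's own figure.** Inputs from the Sample size section: SC mean 65, SD 20, relative difference 20%, power 90%, 5% level (taken as two-sided), dropout 20%.
- Difference: 0.20 × 65 = 13 points.
- The normal-approximation formula gives 50 per arm (power 90.1%).
- 50 / 0.8 = 62.5, rounded up to 63 per arm, 126 in all. The stated figure is reproduced.

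At 20% loss, 0.2 × 126 ≈ 25 families lack a score and about 50 per arm remain. The unadjusted 95% half-width is 1.96 × 20 × √(2/50) = 7.8 points, against 1.96 × 20 × √(2/63) = 7.0 with everyone. The allowance covers precision; it does nothing about bias.

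**2. Bias by hand.** For an unadjusted comparison of observed families,

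bias = m_E × g_E − m_C × g_C,

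where m is the fraction missing in an arm (E = EIP, C = SC) and g is the observed mean minus the missing mean. The document gives no value for g, so these are assumptions:
- 20% missing in each arm, gap of 5, 10 or 20 points in EIP only: 0.2 × g = +1, +2 or +4.
- The same gap in SC only: −1, −2 or −4.
- The same gap in both arms: 0.

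**3. Simulation of the planned regression.** Inputs from the document: 63 per arm, SD 20, difference 13, about 20% lost. Assumed: correlations of 0.5 (baseline with 6 months), 0.4 (baseline with 12 months) and 0.7 (6 with 12 months), and loss that follows a logistic model on the 6-month score relative to the arm's own mean, with slope 1 per SD in the one-arm rows. Average 12-month estimates, true value 13:

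| Loss depends on the 6-month score in | Timing of loss | Planned regression | Likelihood estimate using 6-month scores |
|---|---|---|---|
| Neither arm | after month 6 | 12.9–13.1 | 12.9–13.1 |
| Both arms equally | after month 6 | 13.0–13.1 | 13.0–13.1 |
| SC only | after month 6 | 11.2 | 13.0 |
| EIP only | after month 6 | 14.8 | 13.0 |
| SC only | half before month 6 | 11.1 | 12.2 |
| SC only | all before month 6 | 11.2 | 11.2 |

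The one-arm shifts are 13.0 − 11.2 = 1.8 and 14.8 − 13.0 = 1.8 points, or 1.8 / 13 ≈ 14% of the true difference. A repeat run for this write-up, with the same correlations, slope and 20% loss, agreed with the table to within about 0.2 points.

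**4. Sensitivity to the assumptions.**
- Correlations of 0.5, 0.5 and 0.6: 14.3 for loss in EIP only and 15.5 for opposite directions in the two arms. The estimate using 6-month scores stays at 12.9–13.0.
- Loss that depends in both arms on the absolute score, not on the score relative to the arm mean: about 12.4, against 13.1 with the 6-month scores. No bias in the equal case therefore means equal relative to each arm's mean.

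**The case against.** The strongest reply is that this is a known limitation of a common method in a pilot. The quality-of-life result is labelled preliminary, no tests are planned, and the article admits that its small size limits what can be learned about impact. A shift of 1.8 points is about half of the estimate's own standard deviation (roughly 3.6), and the gain in precision from the alternative is only 2–3%. The mechanism, timing and correlations are all assumed. The scenario in which every loss follows month 6 and depends on the 6-month score is the one most favourable to a repeated-measures model. All of this stands and limits the weight of the point. It does not remove it, because the method is fixed in the text and the better one costs almost nothing.

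Four stronger readings are tempting but not supported:
- *The 6-month data of later dropouts are thrown away.* They are not. They enter the 6-month comparison and go unused only at 12 months.
- *The trial is short of power through dropout.* It is not. The 126 already includes the 20%, which is a planning allowance and not a forecast for each visit.
- *SC families are left without contact.* Both arms get follow-up calls and home assessments. Only contact linked to the programme differs.
- *Deaths are mishandled.* The article does say "Children with NDI and particularly those with seizure disorders and difficulties with swallowing are at increased mortality risk", but rules for scores absent through death are commonly left to an analysis plan, which is not shown here. The article has all deaths reported. A mixed model would itself treat such scores as missing at random, so it is no answer to that question.

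**Conclusion.** The point holds in a limited form. The stated rule and model make each visit's comparison an available-case analysis. At 12 months, the time point of the hypothesis, this leaves collected information unused. If loss after month 6 depends on the 6-month score in one arm only, the 12-month difference is biased by about 2 points on a true 13, given about 20% loss and correlations of 0.5, 0.4 and 0.7. The direction cannot be known in advance: the estimate falls if the selective loss is in SC and rises if it is in EIP. With equal loss relative to each arm's mean there is no bias.

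A reader might infer that the planned result is wrong, or biased against the intervention. The document supports neither, since it gives no mechanism, timing or differential rate of loss. This is an inexpensive improvement to a stated method, not a flaw that invalidates the trial.

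**What to change.** For PedsQL and the other continuous outcomes, replace the two separate regressions with one likelihood-based linear mixed model for repeated measures at 6 and 12 months. Include arm, time, arm-by-time, baseline-by-time and centre, and report the arm difference with its 95% CI at each visit. Include every randomised family with at least one follow-up score, analysed as randomised, and describe the analysis set in those words beside the intention-to-treat label.

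The cost is a change of wording and a standard model. No imputation is needed, so the stated rule is kept. N stays at 126 and no new data are collected.

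State the limits alongside it:
- The model is slightly harder to explain.
- It assumes missing at random.
- Families with no follow-up score remain outside it, and it does not correct for loss before month 6.
- It does not correct for loss driven by unseen 12-month scores.
- It does not settle how to treat scores absent because of death.

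### Only the EIP arm is treated in groups of 6–10 families, yet neither the sample size nor the stated regression models allow for programme-induced correlation within those groups

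*Protocol article*

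**What the plan says.** The Randomisation section allocates each infant and caregiver individually, 1:1, stratified by recruitment centre. Under Intervention arm, "Each EIP group involves 6–10 families; groups are selected depending on locality for ease of attendance". The same section describes group members sharing experiences and working out solutions together, led by expert-parent facilitators. The section on fidelity and adherence adds that "All trial intervention groups will be co-facilitated by a master facilitator". The Standard care arm section describes existing local services, with no groups.

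The Sample size section states that "this sample size will give 90% power to detect a minimal relative difference of 20% on PedQL Family Impact score", "at 5% significance level", "assuming a mean PedQL score of 65 in the SC arm and SD of 20 in both arms", after a 20% dropout allowance. It mentions no ICC, group size or design effect.

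For the third primary outcome (family quality of life) and the secondary outcomes, the Statistical analysis section plans differences with 95% confidence intervals and no formal tests. "Regression models (linear regression for continuous outcomes, logistic regression for binary outcomes) will be used to adjust comparisons for baseline measures of the outcomes", with the aim of better precision. No EIP-group term or cluster-robust variance is named.

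**The concern.** This is a partially nested design: individual randomisation, with group treatment in one arm only. Working through problems together in a stable group is how the programme is meant to act, so some within-group similarity in family quality of life is plausible. Ordinary linear or logistic regression treats EIP families as independent. With a positive programme-induced ICC, it understates the variance of the EIP-arm estimate and hence of the difference between arms.

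For these outcomes the confidence interval is the only planned quantitative inference on effect, so its width has to be right. The article also says the data will inform a larger trial. An over-precise effect and no ICC estimate would serve that purpose poorly.

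**Working it through.** **Inputs from the Sample size section.** Standard-care mean 65 and a relative difference of 20%, so d = 0.20 × 65 = 13 points; SD 20 in both arms; alpha 0.05 (taken as two-sided, since this is not stated); power 0.90; dropout 20%; "The trial will recruit 126 children and their caregivers, 63 per arm". From the Intervention arm section: group size m = 6–10, so 63 families make about 63/10 = 6.3 to 63/6 = 10.5, that is about 7–10 groups. **Assumed, not in the documents:** the ICC.

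**Step 1: reproduce the plan's figure with independent families.**
n per arm = 2 × (1.96 + 1.2816)² × 20² / 13² = 49.7, so 50 evaluable. 50/0.80 = 62.5, so 63 per arm and 126 in total. Power with 50 per arm is 90.1% (89.6% by the noncentral t). The stated size is reproduced exactly at a design effect of 1, with almost no slack.

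**Step 2: add clustering in the EIP arm only.**
DE = 1 + (m − 1) × ICC
SE of the difference = 20 × √((1 + DE)/50)
Power = Φ(13/SE − 1.96)
Ratio of true to naive SE = √((1 + DE)/2)
Actual coverage of a nominal 95% interval = 2Φ(1.96/ratio) − 1

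Example, ICC 0.05 and m = 8: DE = 1.35; SE = 20 × √(2.35/50) = 4.34; power = Φ(13/4.34 − 1.96) = 85.0%; ratio = √(2.35/2) = 1.084; coverage 92.9%.

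| Assumed ICC | DE, m = 6 / 8 / 10 | Unadjusted power | SE ratio | Coverage |
|---|---|---|---|---|
| 0 | 1 / 1 / 1 | 90.1% | 1.00 | 95.0% |
| 0.01 | 1.05 / 1.07 / 1.09 | 89.4 / 89.2 / 88.9% | 1.01–1.02 | 94.7 / 94.6 / 94.5% |
| 0.05 | 1.25 / 1.35 / 1.45 | 86.5 / 85.0 / 83.6% | 1.06–1.11 | 93.5 / 92.9 / 92.3% |
| 0.10 | 1.50 / 1.70 / 1.90 | 82.8 / 79.9 / 77.0% | 1.12–1.20 | 92.0 / 90.8 / 89.6% |

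If the 20% dropout falls evenly, a group of 8 leaves 6.4 evaluable. Then ICC 0.05 / 0.10 / 0.15 gives DE 1.27 / 1.54 / 1.81, power 86 / 82 / 78% and coverage 93.4 / 91.8 / 90.2%.

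**Step 3: effect of the planned baseline adjustment on power.** The sample size does not count this gain. Let r be an assumed baseline–outcome correlation. If adjustment scales the whole variance by 1 − r², power is:
- r = 0.5: 93.3% (ICC 0.05, m = 8) and 87.6% (ICC 0.10, m = 10);
- r = 0.3: 88.2% and 80.8% for the same two cases.

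**Step 4: effect of the adjustment on the intervals.** Group effects produced by the programme arise after baseline, so adjustment removes variance between individuals but not between groups. Take ICC 0.10, m = 6.4 and r = 0.5. The residual variance is 1 − 0.25 = 0.75 of the total, so the residual ICC is 0.10/0.75 = 0.133 and DE = 1 + 5.4 × 0.133 = 1.72. The SE ratio is √(2.72/2) = 1.17, against 1.13 unadjusted, and coverage is 90.7%, against 91.8%. On this reading step 3 is also slightly optimistic. For ICC 0.10, m = 10 and r = 0.5, DE = 1 + 9 × 0.133 = 2.20, SE = 20 × √(0.75 × 3.20/50) = 4.38, and power is Φ(13/4.38 − 1.96) = 84%, not 87.6%.

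**The case against.** Several points on the other side stand.

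- **The ICC is unknown.** The documents give none, and at 0.01 the effect is trivial. The shared manual, common training and a master facilitator in every group may keep groups alike and the ICC low.
- **Shared locality is not the problem.** Families are randomised individually, so correlation by locality is present in both arms and does not invalidate the ordinary SE. In a simulation of 100 families in 8 localities, with site-stratified randomisation, locality ICCs of 0.05–0.15 and no programme-induced effect, ordinary regression covered 94.6–95.4%. Only correlation created by the programme counts.
- **Power may be recovered.** Baseline adjustment was left out of the sample size and could bring power back to 90% or above.
- **The scope is limited.** Feasibility is judged by recruiting 126, and acceptability by protocol violations and attendance, both with qualitative data. Clustering touches neither. The article already says that small size limits what can be learned about impact.
- **The analysis plan is not shown.** It could add a group term, since the word regression does not exclude one.

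These points make the concern conditional but do not remove it. Adjustment does not repair the intervals (step 4). A separate analysis plan could change the model but not the basis of the published 90%. The models described, followed as written, contain no allowance for groups.

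**Conclusion.** The point holds in conditional form. The sample size and the stated models make no allowance for correlation within EIP groups. Any positive programme-induced ICC makes the intervals for family quality of life and the secondary outcomes too narrow and puts unadjusted power below 90%. The effect is negligible near ICC 0.01 and becomes material from about 0.05 (table in the working). The sizes rest on an assumed ICC, 50 evaluable families per arm, a total SD of 20 in both arms, equal group sizes and a normal approximation.

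A reader might infer more: that the intervals are certainly too narrow, or that 90% power is certainly not delivered. The documents support neither, because they give no ICC and because the uncounted baseline adjustment may restore power. Nor does all of the trial's inference rest on these intervals; two of its three primary outcomes do not use them.

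**What to change.** **Data.** Record an EIP group identifier for each family. Attendance at group sessions is already recorded, so this is one added field.

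**Continuous outcomes.** Fit a partially nested linear mixed model with a random group effect in the EIP arm only, standard-care families as singletons, recruitment centre and the baseline outcome as fixed effects, and Satterthwaite or Kenward-Roger degrees of freedom. The centre term keeps urban–rural differences from being counted as group variance.

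**Binary outcomes.** Use a corresponding logistic mixed model, or cluster-robust standard errors with a small-sample correction. The degrees-of-freedom methods above belong to the linear model.

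**Reporting.** Give the ICC with its confidence interval, and note that with about 7–10 groups it will be imprecise.

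**Sample size section.** State that 90% is the unadjusted power assuming ICC = 0, and give the power range over assumed ICCs.

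**Cost.** Slightly wider intervals and a slightly lower stated power; no extra participants.
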